### Sample Size Calculation

Previous studies show that the average number of caries lesions in Dutch children at the age of 5 years is 4.5 (SD 4.5) [12]. This information was used for study size estimation using G*power 3 [34]. This showed that the intervention group needed at least 149 participants to demonstrate a reduction in cumulative caries incidence of at least 30% with a statistically significant Mann-Whitney *U* test allowing for statistical power (1-β) of .8 and a 2-sided α of .05 as a threshold for statistical significance. With an anticipated 30% loss to follow up, the aim was to include at least 200 participants per group.

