## Abstract

**Background:**

Early childhood caries is considered one of the most prevalent diseases in childhood, affecting almost half of preschool-age children globally. In the Netherlands, approximately one-third of children aged 5 years already have dental caries, and dental care providers experience problems reaching out to these children.

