## Introduction

Dental caries (or tooth decay) represents a major public health problem affecting almost half of preschool-age children worldwide [1]. Early childhood caries (ECC) may have severe consequences on daily functioning and socialization in young children [2,3]. While dental caries is highly preventable with twice-daily toothbrushing using fluoridated toothpaste and limited sugar intake between main meals, compliance with these measures still requires much perseverance and endurance from parents. Noncompliance is often related to a lack of awareness among parents about their role in preventing ECC, a persistent belief that primary teeth are not important for oral health in later life, power struggles with the child, and tiredness of parents and their children [4-6]. As with many behavior-related diseases, dental caries shows marked socioeconomic disparities in all age groups [7,8].

Life-course epidemiology has highlighted that early childhood is critical for developing good oral health [9,10]. Positive oral hygiene behaviors and skills should be introduced early in the child’s life, and parents need to acquire the knowledge to develop proper oral hygiene behaviors and skills [10]. This knowledge about the importance of caries prevention in early childhood contributes to the recommendation to have an early dental visit before the age of 1 year [11]. However, while in the Netherlands parents’ compulsory health care insurance fully covers oral health care for their children up to the age of 18 years, oral health care professionals experience difficulties reaching children below 5 years of age, particularly those with lower socioeconomic backgrounds. As a result, less than half of Dutch children have visited an oral health professional at the age of 4 years, and dentin caries is present in about one-third of Dutch children aged 5 years [12,13]. At the same time, more than 90% of all newborns, including children from low socioeconomic backgrounds, visit well-baby clinics (WBCs) for preventive health care and vaccinations at regular intervals up to the age of 4 years [14]. Therefore, WBCs provide a unique window of opportunity for early oral health promotion.

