### Participants and Eligibility Criteria

This study includes parent-child dyads with children aged 6 to 12 months. The study excludes dyads with (1) children in need of specialized health care for a physical, mental, or medical condition; (2) parents with insufficient knowledge of Dutch; and (3) parents who expected to move outside the region of the WBC within the duration of the study. In the case of twins, only 1 child is enrolled in the study.

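### The planning input of 4.5 lesions (SD 4.5) does not fit the article's one-third caries prevalence, so the 80% power is unsupported for the unselected infants enrolled

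*Protocol article*

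**What the plan says.** Under Sample Size Calculation, the article takes from an earlier study that "the average number of caries lesions in Dutch children at the age of 5 years is 4.5 (SD 4.5", with no restriction to children who have caries. From this it derives at least 149 per group to show "a reduction in cumulative caries incidence of at least 30" percent "with a statistically significant Mann-Whitney" U test, with "statistical power (1-β) of .8" and "a 2-sided α of .05". Allowing for 30% loss, it aims for 200 per group. The Results section reports 402 randomized.

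On prevalence, the Abstract says "approximately one-third of children aged 5 years already have dental caries", and the Introduction says "dentin caries is present in about one-third of Dutch children aged 5 years".

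On who is enrolled: "This study includes parent-child dyads with children aged 6 to 12 months". The three exclusions listed there concern specialized care needs, command of Dutch and plans to move. None concerns caries.

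**The concern.** The mean and SD fix the standardized effect behind the sample size. With both at 4.5, a 30% reduction is 1.35 lesions, or 0.30 SD. That holds only if 4.5 (SD 4.5) describes all children, including those without lesions. If two-thirds of children have a count of zero, as the prevalence statements suggest, the all-children distribution has a lower mean or a larger SD, and the same relative reduction is a smaller standardized effect.

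The Discussion relies on the sample size as ensuring adequate power for the principal endpoint. If the input belongs to a different population from the one enrolled, that assurance has no basis, and a null result could be over-read as evidence of no effect. Correcting the dropout allowance, or relabelling the calculation as one for a lesion count, would leave this input unresolved.

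**Working it through.** **Inputs from the article.** Mean 4.5 and SD 4.5; 30% reduction; Mann-Whitney U; two-sided α .05; power .80; 149 per group; 30% loss; 402 randomized 1:1; prevalence about one-third at age 5.

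**1. The plan's own figure.** d = 0.30 × 4.5 / 4.5 = 0.30. Two-sided at 80% power, this needs 175 per group by normal approximation and 176 by t test. The Mann-Whitney version (t-test n divided by the relative efficiency) needs 184 with a normal parent, 203 at minimum efficiency, 160 logistic and 117 Laplace. None gives 149; a one-sided test with normal parent gives 145. By normal approximation, d = 0.30 has 74% power at 149. That is a separate matter and the point here does not depend on it.

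**2. Do mean, SD and prevalence fit together?** For a count X ≥ 0, Cauchy-Schwarz gives P(X > 0) ≥ mean² / (mean² + SD²).
- With 4.5 and 4.5: 20.25 / 40.5 = 0.50.
- Turned round, SD ≥ mean × √((1 − p)/p). With p = 1/3: 4.5 × √2 = 6.36, and affected children would average 4.5 / (1/3) = 13.5 lesions. With p = 0.40 the SD must still be at least 5.51.

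No choice of distribution removes this.

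**3. Evaluable number.** 402 / 2 = 201 per arm; 201 × 0.70 = 140.7, about 141.

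**4. Reading A (assumption): 4.5 (SD 4.5) is for affected children only, one-third affected.**
- Mean = 4.5 / 3 = 1.5.
- Variance = (4.5² + 4.5²) / 3 − 1.5² = 13.5 − 2.25 = 11.25; SD = 3.35.
- d = 0.45 / 3.35 = 0.134.
- Power for means ≈ Φ(d√(n/2) − 1.96). At n = 141: Φ(1.13 − 1.96) ≈ 20%. At n = 149: 21%.
- Varying prevalence from 30% to 40% gives 19% to 25% at 149.

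**5. Reading B (assumption): 4.5 (SD 4.5) is for all children, but for a wider lesion class with 60% to 80% affected.** The affected mean is 4.5/p and the affected variance is 40.5/p − (4.5/p)². For p = 0.6, 0.7 and 0.8 this gives 7.5 (SD 3.35), 6.43 (SD 4.07) and 5.63 (SD 4.36).

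**6. Simulated Mann-Whitney power.** Zeros plus 1 + negative binomial counts, 3,000 to 4,000 runs, Monte Carlo error up to about 2 points. The 30% cut is placed on prevalence, split equally (a factor √0.7 on each), or placed on counts among affected children.

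| Reading | n per arm | Prevalence | Split | Counts only |
|---|---|---|---|---|
| A, 1/3 affected | 141 | 45% | 20% | 7% |
| A, 1/3 affected | 149 | 47% | 21% | 7% |
| B, 60% affected | 149 | 82% | 73% | 62% |
| B, 70% affected | 149 | 90% | 78% | 56% |
| B, 80% affected | 149 | 96% | 83% | 66% |

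For reading A, a plain comparison of proportions (33.3% against 23.3%) gives 48% at 149 and 46% at 140, close to the prevalence column.

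**7. Keeping 4.5 as the all-children mean with one-third affected.** This means giving up the stated SD. With SD at least 6.36, d is at most 1.35 / 6.36 = 0.212, and power for means is at most 45% at 149 and 43% at 141. In that limiting case, where all affected children have the same count, simulated Mann-Whitney power ran from 48% to 78%.

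**The case against.** A reader might infer that the trial has been shown to have far less than 80% power. The article does not support that. The Introduction's one-third is for dentin caries, while the sample size section speaks of caries lesions, and the Primary Outcome section also scores initial lesions. If 4.5 includes initial lesions, at least half of children could be affected and the two figures could coexist. The clinics serve mainly low to middle socioeconomic areas, so a national prevalence need not apply. On the wider-lesion reading, power reaches or exceeds 80% in several scenarios. This stands, and it makes the shortfall conditional.

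The citations do not settle it. The source given for 4.5 is also cited in the Introduction, but jointly with another and for two facts, so the same threshold cannot be presumed. Against this, the Abstract says dental caries without qualification, and the sample size section names neither a threshold nor a subgroup.

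Two further inferences should be avoided. The article claims 80% for cumulative incidence, not for the secondary dmfs/dmft outcome. And the 7% figure should not be quoted as the trial's power: it leaves prevalence unchanged, whereas the stated target is a cut in incidence. The matching figure on reading A is about 45%.

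Recruitment is closed and all results will carry 95% CIs. That limits the harm but does not supply a basis for the 80%.

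**Conclusion.** The concern holds in a limited form. As printed, a mean and SD of 4.5 for Dutch 5-year-olds contradict a caries prevalence of about one-third; this follows from those three numbers alone. Which reading explains it cannot be decided from the article, so the 80% is unsupported rather than disproved.

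Its size depends on the answer. On the affected-only reading the shortfall is large: at about 141 per arm, some 20% for means and 45% for the rank test on the plan's own target, and less if the effect falls partly or wholly on severity. On the wider-lesion reading, with 60% to 80% affected, the range at 149 per arm is from just under 60% to about 96%. These powers rest on assumed count distributions. They also carry an age-5 figure over to an endpoint at 48 months.

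**What to change.** In Sample Size Calculation, state which children and which lesion threshold 4.5 (SD 4.5) refers to, and reconcile it with the one-third prevalence in the Abstract and Introduction. Then recompute the power at the achieved size (402 randomized, about 141 evaluable per arm after 30% loss) from the all-children distribution for that threshold, zeros included. State whether the 30% reduction is assumed in prevalence, in counts or in both. Until that is done, do not state 80%, and align the Discussion's remark on sufficient power.

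The cost is one clarification, one recalculation and some wording. No participants are added. The downside is that the stated power may become less favourable.

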## Results

The first parent-child dyads were enrolled in June 2017, and recruitment finished in June 2019. In total, 402 dyads have been randomized. Interventions and data collection for all of these dyads will be completed by the end of 2022. Therefore, final results are expected in the first half of 2023.

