Third, it is generally known that RCTs usually include participants with a higher level of education or greater motivation and interest. In anticipation of this, WBCs were selected after consultation with the municipalities to represent neighborhoods with a predominantly low-SEP population. In addition, during participant recruitment, much attention was paid to translating the patient information required by the medical ethics committee, being physically present at the WBCs, designing banners and flyers with accessible information, and providing information by telephone to those interested.

Finally, this study had a relatively long follow-up time compared to most other studies on this topic. Therefore, to ensure sufficient statistical power to detect clinical relevance and statistical significance for the principal endpoint, a 30% dropout rate was taken into account when estimating the initial sample size before the start of the intervention.

Dissemination and implementation of our TOHI approach are planned on different levels and in various directions. The dissemination plans include activities both scientific and practical, and therefore include activities such as publication of the results of the RCT in scientific journals and presentations at conferences, as well as activities in support of national oral health policy and practice. For the dissemination of knowledge to practice, distinctions can be made between dissemination plans on the micro, meso, and macro levels. Activities at the micro level include training courses, education and post–initial education, and online or offline workshops to update oral health professionals with knowledge about preventive oral care from first tooth eruption and provide practical tools. At the meso level, the project group investigated what was needed for sustainable implementation of the TOHI; this will be translated into ready-to-use implementation plans for the practices. At the macro level, the knowledge and results will be shared with local and national politicians, policymakers, and health insurers to examine how oral care for the very youngest individuals can be organized differently and how this should be financed. Finally, it should be noted that we have created a practice network in which, in terms of implementation and maintenance of change of practice, establishing ownership of the TOHI is our main goal.

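### The target of 200 per group does not cover the anticipated 30% loss (149 evaluable needs 213), and 149 itself is not reproduced by the stated inputs

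*Protocol article*

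**What the plan says.** The calculation is in the Protocol article under Sample Size Calculation. Its basis is a mean of 4.5 caries lesions with an SD of 4.5 in Dutch five-year-olds. From this, using G*Power, "the intervention group needed at least 149 participants" in order "to demonstrate a reduction in cumulative caries incidence of at least 30" per cent. The test is a "statistically significant Mann-Whitney *U* test", with "statistical power (1-β) of .8" and two-sided alpha of 0.05. Allocation is 1:1 (Intervention Randomization), so the control group needs the same number.

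The allowance for attrition follows: "With an anticipated 30% loss to follow up, the aim was to include at least 200 participants per group". The Results report the enrolment: "In total, 402 dyads have been randomized". The Discussion, on securing enough power for the principal endpoint, says that "a 30% dropout rate was taken into account when estimating the initial sample size before the start of the intervention".

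The article does not give the parent distribution entered in G*Power, the SD assumed in the intervention arm, or the standardised effect size.

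**The concern.** Two links in the chain from inputs to recruitment target look broken.

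- **From 149 to 200.** If 149 children per group must be analysable and 30% are expected to be lost, 200 is too few. The three figures stand together in one paragraph and are incompatible.
- **From the inputs to 149.** A 30% reduction from a mean of 4.5 with an SD of 4.5 is a standardised difference of 0.30. That normally needs more than 149 per group for 80% power.

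What is at stake is how the result is read. A reader facing a null result would credit the trial with 80% power at the anticipated loss, and the Discussion encourages that. Recruitment closed in June 2019, so the issue is the accuracy of the stated power, not further enrolment.

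**Working it through.** **Inputs.** From Sample Size Calculation: mean 4.5, SD 4.5, reduction 30%, two-sided alpha 0.05, power 0.80, Mann-Whitney U, 149 required, 30% loss, target 200 per group. From Results: 402 randomised, taken here as 201 per group because only the total is given.

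**Step 1: dropout.**

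- Needed: 149 / (1 − 0.30) = 212.9, so 213 per group (426 in total).
- Left from the target: 200 × 0.70 = 140, which is 9 short of 149. The target is 213 − 200 = 13 per group too low.
- Left from actual enrolment: 402 × 0.70 = 281.4, or 140.7 per group. Enrolment is 213 − 201 = 12 per group too low.
- Highest loss that still leaves 149: 1 − 149/200 = 25.5% at the target, and 1 − 149/201 = 25.9% at actual enrolment.
- For comparison, 149 × 1.30 = 193.7. Multiplying by 1.3 and rounding up would give 200, but the article does not say how 200 was reached.

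**Step 2: reproducing 149.** G*Power's asymptotic relative efficiency (ARE) method for the Mann-Whitney test takes N = n × ARE per group, then uses a two-sided noncentral t with df = 2N − 2 and noncentrality d × √(N/2). The ARE is 3/π for a normal parent, 0.864 as the minimum, π²/9 for a logistic and 1.5 for a Laplace parent.

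With a normal parent and d = 1.5/4.5 = 1/3 (4.5 to 3.0, a 33.3% reduction), the required n is exactly 149, with power 0.8001. On that same calculation, power at n = 140 is 0.775.

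**Step 3: the stated 30%.** 4.5 × 0.70 = 3.15, a difference of 1.35. With a common SD of 4.5, d = 1.35/4.5 = 0.30.

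| Parent | n per group for 80% | Power at 149 | Power at 140 |
|---|---|---|---|
| Normal | 184 | 71% | 69% |
| Minimum ARE | 203 | 67% | 64% |
| Logistic | 160 | 77% | 75% |
| Laplace | 117 | 89% | 87% |

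A t test at d = 0.30 needs 176. No row gives 149.

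**Step 4: alternatives that come near 149 with a 30% reduction.**

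- If the intervention SD shrinks with the mean to 3.15, the pooled SD is √((4.5² + 3.15²)/2) = 3.88 and d = 1.35/3.88 = 0.348. That needs 138 (normal) or 152 (minimum ARE).
- A one-sided test at d = 0.30 with a normal parent needs 145, but the article states two-sided alpha.

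**The case against.** The dropout arithmetic has no good defence. Writing the target as a minimum does not help, because enrolment ended at 402. The intention-to-treat principle and the missing-data scenarios under Design of Data Analyses do not restore lost information. It is fair to say that the Discussion is not wholly false: an allowance was made, but too small a one. It is also fair that this error alone is modest, about 2.5 points of power.

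The case is stronger on 149. A reader might infer that the trial was really powered for a 33% reduction and has only 69% power for 30%. The documents do not establish either statement. Both depend on a normal parent, on a common SD of 4.5, and on reading a reduction in cumulative caries incidence as a reduction in mean lesion count. With an SD equal to the mean, an SD that falls with the mean is at least as natural as a constant one, and with the minimum ARE it gives 152, close to 149. Lesion counts are also likely to be skewed, so none of the four parents is established as correct; across them, power at 140 runs from 64% to 87%. The G*Power inputs may stand in the full protocol, which is not shown.

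What survives is narrower: under a common SD of 4.5 no standard parent gives 149 for a 30% reduction, and the article does not state the inputs that would.

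**Conclusion.** The dropout allowance is wrong as written. It needs no assumption beyond 1:1 allocation and the article's own figures: 213 per group were needed, and 200 or 201 leave about 140. The target of 149 survives only if loss is at most about 26%, which is below the anticipated 30%. Power at 30% loss is below the stated 80%; it is about 77.5% on the one calculation that reproduces 149 exactly (normal parent, d = 1/3). The article gives no observed loss, so it does not follow that the final analysis will fall short by this amount.

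The second part is a failure to reproduce. With mean 4.5, common SD 4.5, a 30% reduction, two-sided 0.05 and 80% power, the requirement is 184, 203, 160 or 117 per group according to parent, never 149. The 33% reduction is the best single match and a likely origin, but unproven. The 69% figure for a 30% reduction holds only under a normal parent with common SD 4.5. The words at least 30% do not close the gap, since power has to hold at the smallest effect named.

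**What to change.** In Sample Size Calculation:

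1. State that at the anticipated 30% loss about 140 per group remain of the 402 randomised, that 149 is met only if loss is at most about 26%, and that power at 140 is below 80% (about 77.5% on the normal-parent, d = 1/3 calculation that gives 149).
2. Report the standardised effect size, the SD in each arm and the parent distribution that yield 149.
3. Only if these prove to be d = 1/3 with a normal parent, replace the 30% reduction by 33% and add that power for a 30% reduction with common SD 4.5 is about 69% at 140 per group. If they are something else, report the power that follows from them.

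In the Discussion, say that the 30% dropout was only partly allowed for.

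The cost is wording and a look at the original G*Power inputs. No further enrolment is asked for, and allocation, endpoint and analysis are unchanged. The price is a lower stated power.

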### Intervention Randomization

With a 1:1 ratio, participating parent-child dyads were individually allocated to the intervention or control group. This allocation of the TOHI as an add-on to usual care was stratified for each WBC (9 in total) and educational level of the mother (classed as low, medium, or high) as an indicator of SEP. A computerized random sequence generator [35] with a block size of 4 to ensure equally filled strata in each group was used to allocate the intervention status to predefined unique ID numbers. Accordingly, an intervention allocation file was prepared, including intervention codes with blocked series of ranked unique participant IDs for the strata.

### Informed Consent and Concealment of Intervention Allocation

Research nurses who were not involved in the intervention allocation determined the eligibility of parent-child dyads attending the selected WBCs. First, all eligible dyads received verbal and written information about what participation in the study entailed. Then, the parents or persons with parental legal authority signed the informed consent form to confirm voluntary participation. Upon receipt of this form, the principal investigator assigned a unique patient ID based on the WBC and education level of the mother. The corresponding intervention status was retrieved from the prepared allocation files of an independent data administrator. Next, the principal investigator contacted the parents to inform them about the allocated intervention and to ensure that they understood all the information about their participation.

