### Materials Used for the TOHI

A penlight and disposable materials (eg, cotton rolls to dry elements, dental mirrors, and wooden toothpicks to detect dental plaque on elements) were used for oral assessments by the OHC. In addition, the OHC used predefined paper patient records to ensure efficient and uniform reporting. These paper records contained age-related oral health topics to discuss, a caries risk assessment according to the NOCTP protocol, and an assessment of the parents’ oral health behavioral stage. The final caries risk and behavioral stage guided the OHC to follow-up actions, such as which mediating determinants from the HAPA should be addressed with the intervention (Multimedia Appendix 2). Parents in the intervention group received a specially developed TOHI booklet at baseline. This booklet was developed for 2 reasons. First, it contained oral health reports for each appointment with the OHC, which effectively communicated the child’s caries risk to the parents. These reports also covered agreed self-care actions to reduce caries risk. Together with the parents, the OHC examined and recorded the barriers to self-care actions and the mediating determinants of self-efficacy, action planning, and coping planning in these reports (Multimedia Appendix 3). Finally, the booklet covered essential oral health information and provided tips and tricks that the OHC could refer to.

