**Interventions**					
	Toddler Oral Health Intervention performed at ages 6-8, 11, 14-15, 18, 24, 30, and 36 months		✓	✓	✓
	Care as usual		✓	✓	✓

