**Secondary outcomes**					
	Clinical assessment of average number of decayed, missing, and filled surfaces and teeth with Merged International Caries Detection and Assessment System			✓	✓
	Clinical assessment of person time at risk for first cavity with Merged International Caries Detection and Assessment System and incidence density			✓	✓
	Clinical assessment of consequences of untreated dental caries with the PUFA (visible pulpal involvement, ulceration caused by dislocated tooth fragments, fistula, and abscess) index			✓	✓
	Clinical assessment of presence of dental plaque with Simplified Oral Hygiene Index, 6-surface method [41]			✓	✓
	Online questionnaire assessment of oral health behavior with self-developed items		✓	✓	✓
	Online questionnaire assessment of psychosocial constructs of the Health Action Process Approach items (action self-efficacy, risk perception, outcome expectancies, intention, action planning, coping planning, and action control), adapted from Gholami and Schwarzer (2014) [42]		✓	✓	✓
	Online questionnaire assessment of oral health–related quality of life with the Early Childhood Oral Health Related Quality of Life [43] scale			✓	✓
	Online questionnaire assessment of child cooperativeness at oral examinations with the Frankl behavior scale [44]			✓	✓

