**Compliance, fidelity, and cost outcome measures**					
	Total care delivered by oral health coach, assessed by frequency and time in minutes as reported by the oral health coach			✓	✓
	Reasons for and number of visits to a dental clinic (other than Toddler Oral Health Intervention), assessed by parent interviews				✓
	Oral health coach mastery of motivational interviewing competencies, assessed by applying Motivational Interviewing Treatment Integrity codes to audio recordings [39]		✓	✓	✓

^a^–T1: screening and allocation.

^b^T0: baseline.

^c^T1: follow-up at age 24 months.

^d^T2: follow-up at age 48 months.

^e^✓: measurement or action performed at this time point.

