### Secondary Outcomes

The average dmfs/dmft number and the caries incidence density (person-time at risk to the first cavity) will be calculated from the merged ICDAS scores. Consequences of untreated dental caries will be measured using the PUFA (visible pulpal involvement, ulceration caused by dislocated tooth fragments, fistula, and abscess) Index [46]. The presence of dental plaque will be determined with the 6-surface method of the Simplified Oral Hygiene Index [41]. Child cooperativeness during the outcome assessments will be documented by clinical assessors using the modified Frankl behavior scale [44].

Behavioral change over time will be assessed based on self-reported oral health behavior and psychosocial constructs from the HAPA, measured with online questionnaires at baseline, age 24 months, and age 48 months. The early childhood oral health–related quality of life will be measured using the Early Childhood Oral Health Impact Scale [43].

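### Baseline behaviour and HAPA scores are taken after allocation, and very probably after parents know their arm, yet they anchor the behavioural change analysis

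*Protocol article*

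**What the plan says.** The section Informed Consent and Concealment of Intervention Allocation gives an ordered chain. Parents are informed and sign consent. Then "Upon receipt of this form, the principal investigator assigned a unique patient ID based on the WBC and education level of the mother", the matching allocation is retrieved, and "Next, the principal investigator contacted the parents to inform them about the allocated intervention". No questionnaire appears in this chain.

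Table 2 has the same order. Consent and allocation are ticked in the column –T1, which its footnote defines as "screening and allocation". The row "Online questionnaire assessment of oral health behavior with self-developed items" and the HAPA row are first ticked in the next column, T0 (baseline), and again at 24 and 48 months.

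Secondary Outcomes says that behavioural change over time will be assessed from self-reported behaviour and "psychosocial constructs from the HAPA, measured with online questionnaires at baseline, age 24 months, and age 48 months". Design of Data Analyses compares the arms at 24 months on changes in the behavioural determinants and on self-reported behaviour, by linear regression. The blinding section says that parents could not be blinded.

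**The concern.** A baseline anchors a change score safely only if the arm cannot have influenced it. These are self-reports of motivation and habit: self-efficacy, risk perception, intention, planning, brushing and diet. Knowing that a coach has been assigned, or that none has, could move such answers in either direction. Intervention parents might answer more favourably in anticipation, or more self-critically because the topic has become salient. Control parents might lower their answers through disappointment.

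If the arms already differ at T0 because of allocation, subtracting T0 removes that difference from the follow-up contrast or adds to it. Parents who know they are controls may also be less likely to return the T0 form, so baseline response could differ by arm.

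**Working it through.** **Order of events.** The article gives no figure to reproduce, so the check sets its passages side by side.

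- Allocation before T0: explicit in Table 2 (–T1, then T0) and consistent with the consent section, where receipt of the consent form sets allocation in motion.
- Disclosure before the T0 form: not dated anywhere. It is the natural reading of a chain that runs from consent to allocation to telling parents, together with a questionnaire that belongs to the following column.
- Booklet or coach contact before the T0 form: not established. The article says "Parents in the intervention group received a specially developed TOHI booklet at baseline", and Table 2 ticks the row "Toddler Oral Health Intervention performed at ages 6-8, 11, 14-15, 18, 24, 30, and 36 months" at T0, but neither gives an order within T0.

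**Which outcomes use a T0 score.** In Table 2 only the behaviour and HAPA questionnaires are outcomes measured at T0 and again later. Cumulative caries incidence is ticked at 48 months only. The other clinical outcomes are ticked at 24 and 48 months. Maternal education is known before allocation, because it determines the ID.

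**Effect on the contrast.** Work in SD units, with equal SD at each time. Let D be the true between-arm difference in level at 24 months, b the between-arm difference at T0 caused by allocation, and ρ the correlation between T0 and 24 months.

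- Change contrast: D − b
- Level contrast at 24 months: D, whatever b is

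**Illustration.** The values of D, b and ρ are assumptions; the documents give none. The sample size is 200 per arm less the anticipated 30% loss: 200 × 0.70 = 140 per arm. This is cautious at 24 months, because the 30% allowance covers the whole follow-up.

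- SE of the change contrast = √(2(1 − ρ)) × √(2/n). With ρ = 0.5 this is 1.00 × √(2/140) = 0.1195 SD.
- Effect detectable with 80% power, two-sided 0.05: (1.96 + 0.84) × 0.1195 = 0.335 SD. With no loss (200 per arm) it is 2.80 × √(2/200) = 0.28 SD.

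With D = 0.30 and ρ = 0.5:

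| Favourable shift b in the intervention arm (SD) | Change estimate (SD) | Power |
|---|---|---|
| 0 | 0.30 | 0.71 |
| 0.05 | 0.25 | 0.55 |
| 0.10 | 0.20 | 0.39 |
| 0.20 | 0.10 | 0.13 |

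A shift of the opposite sign overstates the effect: b = −0.10 gives 0.30 + 0.10 = 0.40 SD.

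**Precision of comparing levels.** The SD of a level is 1 whatever ρ is, so power for D = 0.30 is 0.71. The SD of change is √(2(1 − ρ)) = 1.18, 1.00 and 0.77 for ρ = 0.3, 0.5 and 0.7. With b = 0, power for change is then 0.56, 0.71 and 0.90. Levels are less precise than change only when ρ exceeds 0.5. At ρ = 0.7, a shift of 0.10 already brings power for change down from 0.90 to 0.58, below the 0.71 for levels.

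**The case against.** The strongest objection is that the article never says when the T0 form was completed relative to the contact that disclosed the arm. The ordered chain stands in a section about consent and concealment, which has no reason to mention questionnaires, and the full protocol may give the order. This stands in part: disclosure before completion is a strong inference, not a recorded fact. Allocation before T0 is stated.

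Several stronger readings are tempting, and the documents do not support them:

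- **The intervention had begun before the T0 form.** The T0 tick belongs to one row covering visits over several years, and booklet handover is not dated against the form. The booklet's appointment reports are completed later with the coach, so at handover only its general information could act.
- **The planned model adjusts for contaminated baseline scores.** Design of Data Analyses names the socioeconomic stratum and imbalanced sociodemographic characteristics as covariables, not T0 behaviour or HAPA scores.
- **The article itself calls these baseline scores postrandomisation.** That term is applied to sociodemographic differences.
- **Health literacy, a subgroup factor, is measured after allocation.** No timepoint is given for it, so nothing follows.
- **The caries result is at risk.** It uses no T0 score.

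It can also be said that a favourable intervention shift, or disappointed controls, would make the change analysis conservative for a claim of benefit, and that the Discussion already concedes possible information bias. Both are fair. But the direction is not known, and a general caveat does not alter an analysis of change from T0.

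**Conclusion.** The point holds for the self-reported behavioural and HAPA secondary outcomes. Their T0 scores are post-allocation by the article's own table and very probably post-disclosure. Any shift at T0 caused by allocation passes in full into the change contrast. That part is algebra; whether a shift occurred, how large it was and in which direction are unknown. The figures of 0.05 to 0.20 SD show sensitivity and do not estimate actual bias. They rest on an assumed effect of 0.30 SD, a correlation of 0.5 and 140 per arm. The primary caries outcome, the other clinical outcomes and maternal education are not affected. If completion dates show that T0 forms came before disclosure, the concern is resolved by one clarifying sentence.

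**What to change.** Recruitment closed in June 2019, so the order cannot be changed; the remedy lies in reporting and analysis.

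1. State the actual order of questionnaire, allocation and disclosure, using completion and disclosure dates where they were recorded. The article does not say that disclosure dates were kept.
2. Unless T0 forms are shown to precede disclosure, do not treat T0 scores as pre-randomisation values. Compare 24- and 48-month levels between arms for all participants, adjusted for the randomisation strata (well-baby clinic and maternal education), and report this alongside the change analysis. Adjusting for the T0 score is not a substitute: it would leave a bias of about ρ × b (for example 0.5 × 0.10 = 0.05 SD).
3. Report T0 questionnaire response by arm.
4. Do not analyse subgroups defined by form timing differently, because timing may itself depend on arm.

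The cost is one additional analysis on data already being collected, and some loss of precision where the T0 score is not used.
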